
#### Randomization

After the screening period, the patients return to our center. To ensure that eligible subjects are compliant, we will verify that at least 5 of the last 7 days of the pain diary are completed. This is important because the pain diary of the screening period is used as the baseline measurement of the primary outcome. Randomization is performed using ALEA data management. This software is provided by the Trans European Network for Clinical Trials Services (http://www.tenalea.com/). The randomization is computer- controlled based on the electronic case report form that is used. A blinded message is send to the investigator and an un-blinded message is send to the pharmacy. Patients are stratified based on the type of the *SCN9A* variant ((1) genetic variant and (2) genetically and functionally confirmed) and on the clinical diagnosis of SFN ((1) abnormal skin biopsy, (2) abnormal temperature threshold testing, and (3) abnormal skin biopsy and abnormal temperature threshold).

#### Blinding

The study is subject-blinded and investigator-blinded until the end of the study. Blinding codes are only broken in emergency situations for reasons of subject safety.

The lacosamide and the matching placebo are provided as 50 mg tablets for oral administration. Tablets are provided in containers. Rescue medication (acetaminophen) is provided in its approved marketed product dress. All medication dispensed to the subjects are to be returned to the investigator and double-checked by the monitor to assure study compliance.

#### Compliance

The following compliance calculation will be applied:$$ \%\mathrm{Compliance}=\mathrm{number}\ \mathrm{o}\mathrm{f}\ \mathrm{t}\mathrm{ablets}\ \mathrm{t}\mathrm{aken}/\mathrm{number}\ \mathrm{o}\mathrm{f}\ \mathrm{t}\mathrm{ablets}\ \mathrm{expected}\ \mathrm{t}\mathrm{o}\ \mathrm{have}\ \mathrm{t}\mathrm{aken}\times 100. $$

Subjects are coded as being a noncompliant if the percentage compliance according to the above formula is less than 80 % or greater than 120 % study drug compliance.

### Efficacy measurements

The daily Pain Intensity Numerical Rating Scale (PI-NRS) consists of an 11-point numerical scale ranging from 0 to 10, where 0 represents no pain and 10 the worst pain possible. The subjects are asked to complete the PI-NRS twice daily, in the morning and evening, preferably at fixed time points. In addition, the daily sleep interference scale (DSIS) is completed every day on awakening in the morning. The DSIS consists of an 11-point numerical scale ranging from 0 (pain does not interfere with sleep) to 10 (pain completely interferes with sleep) and is used to determine sleep quality. At each assessment, the following additional questionnaires are completed: the Neuropathic Pain Scale (NPS), Small Fiber Neuropathy Symptom Inventory Questionnaire (SFN-SIQ), Patient’s Global Impression of Change (PGIC), and the generic Short Form (36) Health Survey (SF-36).

### Outcome measurements

The chosen outcomes are largely based on the international criteria advised by the IMMPACT group for measurement of pain [26].

#### Primary outcome

The primary efficacy endpoint is defined as the proportion of patients demonstrating a 1-point average pain score reduction compared to baseline using the PI-NRS. A 1-point change on the PI-NRS is considered the minimum clinically important difference (MCID) according to the unified rule of ½ x standard deviation (SD) and recommendations given by the IMMPACT group [26, 27].

#### Secondary outcome

Secondary outcomes include changes seen in the maximum pain score on the PI-NRS, the NPS, DSIS, PGIC, SFN-SIQ, SF-36, adverse events, laboratory safety tests (e.g., hematology and clinical chemistry), blood pressure (BP), pulse rate (PR), and electrocardiogram (ECG).

Sensitivity analyses include assessing the proportion of patients having ≥ 2 points average pain improvement compared to their baseline PI-NRS scores.

#### Data management

An electronic case report file (eCRF) is used for each patient to collect all data. To host the eCRF, MACRO electronic data capture is used, powered by InferMed Ltd, London, UK. It has been designed to support compliance with the requirements of relevant regulatory bodies including International Council for Harmonisation (ICH) Good Clinical Practice (www.infermed.com). Assessments start at the screening visit. In addition, assessments at site visits and by phone are performed according to the scheme presented in Fig. 1 and include a standardized interview to determine the patient’s clinical condition and well-being, assess the various questionnaires, determine compliance, assess laboratory results, and at predefined moments, perform ECG. During each contact (visit or by phone), adverse events, and concomitant medication are discussed. At each visit, the diary and the remaining medications are collected. A summary of the assessments made during visits and telephone calls is provided in Table 1.

**Table 1 Tab1:** Schedule of assessments throughout the study

Protocol Activity	Screen (Week -4-0)	Base-line/ Randomization	Titration (Week 1-3)		Treatment Period 1 (Week 4- 11)		Tapering Week 12-13	Washout Week 14-15	Titration (Week 16-18)		Treatment Period 2 (Week 19- 26)		Tapering Week 27-28	Follow-up Week 33
Clinic Visit^a^	V1	V2	T1-2	V3	T3-T5	V4	T6	V5	T7-T8	V6	T9-T11	V7	T12	V8
Informed Consent	X													
Inclusion/Exclusion criteria	X													
Randomization^b^		X												
Medical History	X													
Demography	X													
Physical Examination (Full)	X													
Physical Examination (Brief)		X		X		X		X		X		X		
Weight and Height	X													
Safety Laboratory Tests^c^	X			X		X		X		X		X		
FSH^d^	X													
HbA1c blood test^e^	X													
12-lead ECG	X			X		X		X		X		X		
BP (supine and standing) and PR	X			X		X		X		X		X		
Daily Pain Diary (PI-NRS)^f^		X												X
Daily Sleep Interference Scale (DSIS)^g^		X												X
Neuropathic Pain Scale (NPS)	X	X	X	X	X	X	X	X	X	X	X	X	X	
SFN-SIQ Questionnaire	X	X	X	X	X	X	X	X	X	X	X	X	X	
Patient Global Impression of Change		X	X	X	X	X	X	X	X	X	X	X	X	
SF-36		X				X		X				X		
Adverse Event Monitoring^h^		X												X
Concomitant Medication^h^		X												X
Dispense Study Medication^i^		X		X		X		X		X		X		
Retrieve Study Medication dispensed at previous study visit				X		X		X		X		X		X
Dispense Rescue Medication		X		X		X		X		X		X		
Retrieve Rescue Medication dispensed at previous study visit				X		X		X		X		X		X
Dispense and instruct on Daily Pain Diaries	X													
Retrieve Daily Pain Diary	X	X		X		X		X		X		X		X
Study medication compliance check				X		X		X		X		X		X

BP; blood pressure, ECG; electrocardiogram, FSH; follicle-stimulating hormone, HbA1c; hemoglobin A1c, NPS; neuropathic pain scale, PI-NRS; pain intensity numerical rating scale, PR; pulse rate, SFN-SIQ; small fiber neuropathy symptom inventory questionnaire, T; telephone call, V; visit, SF-36; short form 36

^a.^ Visit/study activity window can be ± 2 days

^b.^ Subjects will be randomized provided they fulfill study selection criteria

^c.^ Safety laboratory tests include hematology and clinical chemistry

^d.^ Females who are 45-60 years of age who are amenorrheic for at least 1 year

^e.^ HbA1c test to be performed in subjects with diabetes and at investigator’s discretion for subjects who do not have a clinical diagnosis of diabetes but present with hyperglycemia on safety lab tests

^f.^ Daily Pain Diary (PI-NRS) to be completed by subject twice daily (morning and evening pain scores) and reviewed by study personnel at scheduled clinic visits

^g.^ Daily Sleep Interference Scale (DSIS) to be completed by subject once daily on waking starting morning after Screening Visit (V1)

^h.^ Adverse events and concomitant medication will be monitored during the entire study

^I.^ Full dosing instructions will be provided and the first dose of study medication will be taken on the evening of the SECOND study visit (V2)

Privacy of the patients is guaranteed; stored data and materials are only identifiable to the person by a sequentially assigned subject number. The handling of personal data complies with the Dutch Personal Data Protection Act (De Wet Bescherming Persoonsgegevens, WBP). The SPIRIT checklist and figure for this study protocol are shown in Additional files 1 and 2.

#### Safety reporting

Adverse events are recorded and monitored. The principal investigator is to be informed immediately in case of any serious adverse event (SAE). Every SAE is reported to the Ethics Committee. Suspected unexpected serious adverse reactions (SUSAR) are also reported. Furthermore, all SUSARs are expedited to the competent authorities in other Member States, according to the requirements of the Member States.

### Statistical analysis

#### Sample size

A 1-point change on the average PI-NRS compared to baseline is considered as the MCID [26, 27]. We assume a response rate of approximately 20 % in the placebo-treated group, based on a meta-analysis of the placebo effect in pain studies in which the effect varied from 7-37 %, with a 50 % pain reduction in 16 %. In the lacosamide-treated group, we assume a response rate of approximately 60 % based on the IMMPACT criteria in which the clinical relevant pain reduction may be less than 50 %. Fixing a two-sided alpha at 5 %, a sample size of 22 patients is required per treatment group to show efficacy with 80 % power between the two groups (chi-square test). Assuming a dropout rate of approximately 10 % (two to three patients), a total of 25 subjects will be needed per treatment group (in a parallel study). Since the number of patients with *SCN9A*-associated SFN is limited, a crossover design was chosen to fulfill sample size requirements with the inclusion of 25 subjects.

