#### Type of analysis

The analyses are performed on the intention-to-treat (ITT) population, defined as all patients who received at least one dose of randomized study medication and had at least one post-baseline assessment. Patients withdrawing from the study are considered as nonresponders. The comparison of the proportion of patients in both groups (lacosamide versus placebo) reaching the predefined cut-off is estimated using Kaplan-Meijer serial time series graphs with a log-rank test.

For secondary efficacy endpoints, the treatment differences for change from baseline in selected outcome measures, according to the predefined inquiries, are analyzed using nonparametric tests. The statistical tests used depend on the type of data. Analyses of safety parameters are performed on the safety set (SS), which includes all randomized patients who took at least one dose of trial medication. Individual missing data are assigned using a last observation carried forward approach. Other missing-data treatment methods are performed (for example single and multiple imputation) to test which of these methods is the best according to sensitivity analyses.

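### The stated 80% power belongs to a parallel-group chi-square test, not to the 25-patient crossover or the log-rank test that the protocol plans

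*Protocol article*

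**What the plan says.** The Sample size section of the protocol article fixes a two-sided alpha of 5% and takes 20% responders on placebo ("We assume a response rate of approximately 20 % in the placebo-treated group") and about 60% on lacosamide. It concludes that "a sample size of 22 patients is required per treatment group" and ties that number to a named test: "to show efficacy with 80 % power between the two groups (chi-square test"). With about 10% dropout this becomes 25 per group, which the article attributes to a parallel trial. Because eligible patients are few, "a crossover design was chosen to fulfill sample size requirements with the inclusion of 25 subjects".

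The Study design section confirms two periods, with every patient crossing to the other treatment. The primary outcome is a responder proportion. In Type of analysis, the comparison of the proportions "reaching the predefined cut-off is estimated using Kaplan-Meijer serial time series graphs with a log-rank test", and patients who withdraw count as nonresponders. The article gives no power for a paired comparison or for a log-rank test, and no within-patient correlation or discordance rate.

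**The concern.** Three things that should agree do not: the test that was sized (chi-square on independent groups), the design (each patient observed on both treatments) and the planned test (log-rank). In a crossover with a binary endpoint, a paired test draws its information from patients who respond on one treatment only. Two marginal rates do not fix how many such patients there are. The within-patient association must be assumed as well, and the article assumes none.

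The 80% is the article's justification for 25 patients in a condition where more are hard to find. A null result will be read against that figure, so it should describe the trial being run.

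**Working it through.** **Inputs.** From the Sample size section: placebo response pP = 0.20, lacosamide response pL = 0.60, two-sided alpha 0.05, power 80%, 22 per group, 10% dropout, 25 patients. From Type of analysis: log-rank test, withdrawals as nonresponders. Assumed, because the article gives no value: within-patient correlation of response, phi = 0, 0.2 and 0.4. The largest value possible at these rates is 0.41.

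**1. The article's own figure.** With the arcsine formula, h = 2·arcsin(√0.6) − 2·arcsin(√0.2) = 0.845 and n = 2(1.960 + 0.842)²/h² = 21.99, so 22. The pooled-variance formula gives 22.33, so 23. Exact power of the uncorrected chi-square test at 22 per group is 79.1%. Dropout: 22/0.9 = 24.4, so 25. The stated numbers reproduce for two independent groups.

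**2. Discordant proportions in the crossover.** The proportion responding in both periods is p11 = pL·pP + phi·√(pL·qL·pP·qP) = 0.12 + 0.196·phi, where q = 1 − p. The discordant proportions are 0.60 − p11 (lacosamide only) and 0.20 − p11 (placebo only):

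- phi 0: 0.48 and 0.08
- phi 0.2: 0.44 and 0.04
- phi 0.4: 0.402 and 0.002

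**3. McNemar power.** This is the sum of multinomial probabilities over all discordant counts at which the test rejects. In the second row, 10% of patients are nonresponders in both periods, so the discordant proportions are multiplied by 0.9 (for example 0.432 and 0.072 at phi 0).

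| Setting | Test | phi 0 | phi 0.2 | phi 0.4 |
|---|---|---|---|---|
| 22 completing pairs | exact / mid-p | 67% / 76% | 78% / 86%* | 92% / 97% |
| 25 patients, 10% withdraw | exact / mid-p | 68% / 77% | 79% / 86% | 93% / 97% |

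*85.5% with unrounded discordant proportions.

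The normal approximation for 80% power is n = (1.960√s + 0.842√(s − d²))²/d², with s the sum of the discordant proportions and d = 0.40. It gives 25.0, 21.1 and 17.2 completing pairs at phi 0, 0.2 and 0.4.

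**4. The log-rank test.** Assume proportional hazards, no withdrawals and no allowance for pairing. The hazard ratio is ln(0.4)/ln(0.8) = 4.11. Schoenfeld's formula gives 84% power at 22 per arm and 88% at 25. Simulation with copula correlation from 0 to 0.8 gives 80% to 89% at 22 and 86% to 93% at 25. Under a common response rate of 40% (assumed) and 25 patients, type I error falls from 5.1% at zero correlation to 2.8% at 0.3 and 0.9% at 0.6.

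**5. The dropout step.** A patient counted as nonresponder in both periods is a concordant pair, which McNemar's test ignores just as if the patient had left. Hence the second row of the table is no worse than the first. Even for the parallel test, 25 per group at 0.9 × 60% = 54% versus 0.9 × 20% = 18% has exact chi-square power 79.6%, against 79.1% for 22 per group at 60% versus 20%. If withdrawal is instead unrelated between periods, phi applies to the 54% and 18% margins, and exact power with 25 patients is 65.8%, 76.3% and 90.5%.

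**The case against.** The article does not hide its basis: it names the chi-square test and labels 25 per group as a parallel-trial number. Carrying a parallel per-group number over as the crossover total is a common simplification, and the Discussion calls the trial a pilot. Some positive within-patient correlation is plausible, since both periods are compared with the same screening-diary baseline. At phi of about 0.2, power is near or above 80%. The unpaired log-rank test also reaches at least 80% in simulation. All of this stands. It limits the point to a mismatch that needs restating, but it does not supply the missing power figure.

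A reader might infer three stronger things that the documents do not support:

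- **That the trial is underpowered.** Power below 80% appears at low correlation, especially with the conservative exact test. Higher correlation reverses this, and the article gives no value.
- **That the arithmetic is wrong.** It reproduces for its own model.
- **That raising 22 to 25 fails because withdrawals stay in as nonresponders.** Step 5 shows that the inflation does its job when a withdrawal counts in both periods. A small extra loss arises only if withdrawal is unrelated between periods, and the article does not say which applies.

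**Conclusion.** The point holds as a mismatch between sizing, design and analysis. The 80% is not the power of the planned crossover or of the planned log-rank test, and no stated assumption would let a reader convert it. With 25 patients and 10% withdrawing as nonresponders in both periods, paired power is about 68% to 79% (exact) or 77% to 86% (mid-p) for phi from 0 to 0.2, and 93% or 97% at phi 0.4. These figures take the article's 60% and 20% as true among completers; the phi values are assumptions. The direction of the error is therefore unknown. The low log-rank type I error depends on reading the planned test as ignoring pairing, which the article neither states nor excludes.

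**What to change.** Keep 25 patients. In Sample size and Type of analysis, name the same paired binary test (McNemar, exact or mid-p) as the one that is sized and the one used for the responder endpoint. The Kaplan-Meier curves can remain as description. State the assumed discordant proportions among completers, for example 0.48 and 0.08 at phi 0 and 0.44 and 0.04 at phi 0.2. Say whether a withdrawal counts as nonresponse in one period or both. Replace 80% by the range for the named test: about 68% to 79% for exact or 77% to 86% for mid-p over phi 0 to 0.2, if withdrawals count in both periods.

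The cost is a rewritten sample-size paragraph, a changed sentence on the primary test, settled before unblinding, and a power range in place of a single figure. No patients, visits or data are added.

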#### Type of analysis

The analyses are performed on the intention-to-treat (ITT) population, defined as all patients who received at least one dose of randomized study medication and had at least one post-baseline assessment. Patients withdrawing from the study are considered as nonresponders. The comparison of the proportion of patients in both groups (lacosamide versus placebo) reaching the predefined cut-off is estimated using Kaplan-Meijer serial time series graphs with a log-rank test.

For secondary efficacy endpoints, the treatment differences for change from baseline in selected outcome measures, according to the predefined inquiries, are analyzed using nonparametric tests. The statistical tests used depend on the type of data. Analyses of safety parameters are performed on the safety set (SS), which includes all randomized patients who took at least one dose of trial medication. Individual missing data are assigned using a last observation carried forward approach. Other missing-data treatment methods are performed (for example single and multiple imputation) to test which of these methods is the best according to sensitivity analyses.

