### Study design

The Lacosamide-Efficacy-‘N’-Safety in SFN (LENSS) study is a randomized, placebo-controlled, double-blind, crossover-design study (Fig. 1). The study consists of 2 periods. Before the first period, the screening and baseline measurements takes place. Subjects ulfilling the inclusion and exclusion criteria are subsequently randomized to receive lacosamide or placebo. The first period starts with the first titration period of 3 weeks, in which study the medication (lacosamide or equivalent placebo) will be gradually increased. Subsequently, patients enter the first treatment period of 8 weeks. This period is followed by a 2-week tapering period. After a 2-week washout period, the second period, which is executed in the same manner as the first period, begins. Subjects cross over to the alternate arm and undergo the second 3-week titration period, followed by the second treatment period (8 weeks) and a tapering period (2 weeks). In both treatment periods, subjects receive lacosamide 200 mg b.i.d. or placebo. Patients are examined at the study outpatient site at the entry and at the end of both treatment periods (maximum of eight site visits). In addition, subjects are contacted and interviewed in a standardized manner by phone every 2 weeks to determine clinical condition and well-being, and collect data on safety and side effects. A follow-up visit is performed approximately 4 weeks after the last dose of study medication.

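### The primary log-rank test is one for independent groups, but in this crossover both groups are the same patients; it is conservative rather than inflated, and should be replaced by a within-patient analysis

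*Protocol article*

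**What the plan says.** All places are in the protocol article.

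- **Study design** sets up a two-period crossover: "Subjects cross over to the alternate arm and undergo the second 3-week titration period". Each patient receives both treatments.
- **Primary outcome** is a responder proportion: "the proportion of patients demonstrating a 1-point average pain score reduction compared to baseline using the PI-NRS".
- **Randomization** states that "the pain diary of the screening period is used as the baseline measurement of the primary outcome". No separate baseline for the second period is named.
- **Type of analysis** compares the lacosamide and placebo groups on the proportion "reaching the predefined cut-off is estimated using Kaplan-Meijer serial time series graphs with a log-rank test". It mentions no pairing, no stratification by patient, and no period or sequence term.
- **Sample size** assumes two rates: "We assume a response rate of approximately 20 % in the placebo-treated group" and "we assume a response rate of approximately 60 % based on the IMMPACT criteria". It derives 22 per group for 80% power by a chi-square test, raises this to 25 for dropout in a parallel design, and then uses 25 patients in total because each serves in both groups.

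**The concern.** The log-rank variance treats the two sets of outcomes as coming from different people. Here they come from the same people, apparently scored against the same baseline, so a positive correlation between a patient's two results is to be expected. The variance then includes between-patient variation that cancels in a within-patient comparison. The p-value no longer has its stated error rate, and part of the gain from the crossover, chosen because eligible patients are few, is given up.

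The test also takes no account of period. By Table 1 the first titration starts in week 1 and the second in week 16, so the periods start 15 weeks apart.

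This is not a detail left to an analysis plan. The article names the primary test, and the named test does not match the design.

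**Working it through.** **1. The plan's own figure.** Inputs from Sample size: 20% and 60%, two-sided alpha 5%, power 80%. The mean rate is 0.40.

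n = [1.96·√(2·0.4·0.6) + 0.842·√(0.2·0.8 + 0.6·0.4)]² / 0.4² = (1.358 + 0.532)² / 0.16 = 22.3, which rounds up to 23. At 22 per group the power is 79.4%. Dropout: 22/0.9 = 24.4, so 25. The stated 22 and 25 are reproduced within rounding, but as an independent-groups calculation.

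**2. Why the error rate moves.** Take the simple difference in proportions, with a common rate p and a correlation φ between a patient's two binary results. The true variance is 2p(1−p)(1−φ)/n. An unpaired test uses 2p(1−p)/n. The true two-sided error is therefore about 2[1 − Φ(1.96/√(1−φ))].

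A latent normal correlation ρ gives φ = (2/π)·arcsin ρ exactly at a rate of one half, and close to that at 40%.

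- ρ = 0: φ = 0, error 5.0%
- ρ = 0.3: φ = 0.19, 1.96/√0.81 = 2.18, error 2.9%
- ρ = 0.5: φ = 0.33, 1.96/√0.67 = 2.40, error 1.6%
- ρ = 0.7: φ = 0.49, 1.96/√0.51 = 2.75, error 0.6%

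**3. Simulation of the log-rank itself.** Assumptions, none of them given in the article:

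- 22 completers;
- exponential response times on a weekly grid over 11 weeks (3 titration plus 8 treatment), with nonresponders censored at week 11;
- latent within-patient correlation ρ;
- no period effect.

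With 3,000 runs per cell the Monte Carlo error is about 0.4 points at 5% and 0.7 points at 80%. Type I error is at 40% in both arms, and power is at 60% versus 20%.

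| ρ | Log-rank error (nominal 5%) | Log-rank power | Mid-p McNemar error | Mid-p McNemar power | Patient-stratified log-rank power |
|---|---|---|---|---|---|
| 0 | 4.2–4.9% | 81% | 3.6% | 76% | 66% |
| 0.3 | 2.6–3.1% | 84% | 4.7% | 84% | 75% |
| 0.5 | 1.3–1.7% | 86% | 3.3% | 89% | 83% |
| 0.7 | 0.3–0.7% | 87% | 2.6% | 94% | 92% |

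The error ranges in the second column come from repeated runs. Repeats of the log-rank power ran from 78% to 88%. At ρ = −0.3, an unlikely case here, the log-rank error was 6.7%.

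**4. Why power survives at the planned effect but not at a smaller one.** The unpaired test needs an observed difference of about 1.96·√(2·0.4·0.6/22) = 0.29. The planned difference of 0.40 lies above that, so the smaller true variance under positive correlation raises power.

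The placebo range quoted in Sample size reaches 37%. At 60% versus 37% the difference is 0.23, the mean rate is 0.485, and the threshold is 1.96·√(2·0.485·0.515/22) = 0.295. The difference is now below the threshold, so positive correlation lowers power. By simulation at ρ = 0.7 it is about 30% unpaired against 47 to 53% for paired tests.

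**The case against.** The strongest defence is that the test delivers what Sample size promises. At 60% versus 20% its power is about 80% or more for every non-negative correlation tried. The error is in the safe direction, so a significant result would stay credible. Some paired alternatives do worse: an exact Mainland-Gart test has about 61 to 81% power at the planned effect, with a true error of about 2% or less. All of this stands, and it limits the severity.

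It can also be said that the article never states that periods are treated as independent patients, and that a log-rank stratified by patient would be compatible with its wording. That is fair as to intention. But the sentence names a comparison of two groups by a plain log-rank test, and Sample size reasons in the same independent-groups terms, so the test as written is the unpaired one.

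A reader might infer three stronger things that the documents do not support:

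- **That the true error is far below 5% as a fact.** Its size depends on a correlation the article does not give; at zero correlation the error is close to nominal.
- **That the 80% power is lost.** At the planned rates it is not.
- **That a period effect biases the result.** With balanced sequences, ignoring period mainly costs precision. Bias needs unequal sequences or dropout, and no period effect was simulated.

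**Conclusion.** The point holds in a limited form. The stated primary test assumes independent groups, whereas the two groups are the same patients. Over an assumed correlation of 0 to 0.7 its true type I error runs from about 4 to 5% down to below 1%. The consequence is a conservative test, not false positives.

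At the planned effect with 22 completers the paired mid-p test is weaker at zero correlation, about equal at 0.3, and better from about 0.5. The loss from not pairing is larger if the placebo response is nearer 37% and the correlation is high. These figures rest on the assumed correlation, response-time model and number of completers; the effect of ignoring period is not quantified. Severity: should be fixed.

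**What to change.** In Type of analysis, before unblinding, replace the unpaired log-rank as primary test with a within-patient analysis of period response. Two options are suitable:

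- conditional or mixed logistic regression with treatment and period; or
- a mid-p McNemar test, which is simpler but has no period term.

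Report the paired difference in proportions with its 95% confidence interval. Keep the Kaplan-Meier curves as description, and stratify any retained log-rank by patient. Do not make the exact Mainland-Gart test primary, given its power above.

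No new patients or data are needed, but the change is more than wording. The power statement in Sample size should be restated for the paired test as a range over the assumed correlation: about 75 to 94% for the mid-p test at 22 completers. It could fall slightly below 80% if the correlation is near zero. The logistic models were not simulated here, so their error rate and power at this sample size should be checked before one is fixed as primary.

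### LOCF is neither confined to the treatment period nor ranked against the nonresponder rule, and sensitivity analyses are asked to find the best imputation method

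*Protocol article*

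**What the plan says.** The protocol article, under Type of analysis, gives three statements on missing data.

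- Beside the primary responder comparison: "Patients withdrawing from the study are considered as nonresponders". The abstract repeats this rule.
- After the secondary and safety analyses: "Individual missing data are assigned using a last observation carried forward approach". No endpoint and no treatment period is named.
- Other methods, with single and multiple imputation as examples, are then run "to test which of these methods is the best according to sensitivity analyses". No criterion for *best* is given, and nothing says that LOCF stays the primary method whatever these runs show.

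The intention-to-treat set is "all patients who received at least one dose of randomized study medication and had at least one post-baseline assessment". A patient can therefore be in it without ever starting period 2. The design is a two-period crossover (Study design): "Subjects cross over to the alternate arm and undergo the second 3-week titration period". The primary endpoint is "the proportion of patients demonstrating a 1-point average pain score reduction compared to baseline using the PI-NRS".

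**The concern.** There are three weaknesses, the first being the most important.

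1. **Choice of method.** No analysis of the observed data can tell which imputation came closest to values nobody recorded. Comparing methods shows only whether the conclusion moves. A plan that looks for the best method this way, with no criterion and an open list of candidates, leaves room to prefer a method after its result is known. That weakens error control in a trial of 25 patients.

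2. **Carrying across periods.** In a crossover the last available value may belong to the washout, the taper or the other treatment. If it is entered as a period 2 value, the within-patient treatment difference is no longer a comparison of the two treatments.

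3. **Precedence.** A patient who withdraws while at least 1 point below baseline is a nonresponder under one sentence and could be a responder under the other. The plan does not say which sentence governs.

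**Working it through.** **Inputs from the plan.** Sample size section: 25 subjects, about 10% dropout (two to three patients), response rates of 20% on placebo and 60% on lacosamide, two-sided 5% alpha, 80% power, 22 per group. Table 1: the visit schedule.

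**The plan's own figures.** The pooled two-proportion formula, with mean proportion 0.40, gives n = [1.96·√(2·0.4·0.6) + 0.842·√(0.2·0.8 + 0.6·0.4)]² / 0.4² = 22.3, so 23 when rounded up. Power at 22 is 79.4%. Both agree closely with the stated 22 and 80%. Dropout: 22/0.90 = 24.4, so 25 as stated, and 0.10 × 25 = 2.5, which is the stated two to three patients. None of this is disputed.

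**What LOCF can carry for SF-36.** Table 1 collects it at V2 (baseline), V4 (end of treatment period 1), V5 (washout) and V7 (end of treatment period 2). If V7 is missing:

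| Last SF-36 available | Value entered for V7 | Period 2 minus period 1 difference (same baseline for both periods) |
|---|---|---|
| V5 | washout score | V5 − V4: washout against the period 1 treatment |
| V4 | score on the other treatment | V4 − V4 = 0, whatever the true effect |
| V2 | baseline score | V2 − V2 = 0, since V4 is then also filled from V2 |

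No row holds a score obtained on the period 2 treatment. NPS, SFN-SIQ and PGIC are collected more often, including by telephone in titration and treatment. For them the problem arises for gaps at the start of period 2, filled from V5 or from T6 in the taper, and for patients who never start period 2. The SF-36 case takes Table 1 as the operative schedule. The Efficacy measurements section lists SF-36 among the questionnaires completed at each assessment. If that governed, period 2 scores would exist to carry and only the more limited problem would remain.

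**Size of the precedence question.** With 60% response among completers and 10% withdrawals, the lacosamide rate is 0.60 × 0.90 + c × 0.10, where c is the share of withdrawals whose carried score meets the cut-off.

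- Nonresponder rule (c = 0): 54%
- LOCF with c = 0.6: 60%, a shift of 1.5 patients in 25
- LOCF with c = 1: 64%, a shift of 2.5 patients

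The range is 0 to 10 percentage points, and it arises only if LOCF were applied to withdrawals on the primary endpoint.

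**Size of the method choice.** Null simulation of a 25-patient crossover: 4,000 runs, Wilcoxon signed-rank test on a continuous outcome, values missing at random and independently in each period. Assumptions not in the plan: SD 2, between-period correlation 0.5, within-period correlation 0.7. The candidates were LOCF, baseline carried forward and single stochastic regression imputation. Entries are type I error at nominal 5%.

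| Missing per period | LOCF | Baseline carried | Single regression | Smallest p of three |
|---|---|---|---|---|
| 10% | 4.7% | 4.5% | 5.7% | 7.6% |
| 20% | 5.1% | 4.6% | 7.3% | 10.0% |
| 30% | 4.3% | 5.0% | 7.9% | 11.2% |

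Part of the excess comes from single imputation itself. Measured against that column (unrounded), selection adds 7.625 − 5.65 = 2.0, 10.025 − 7.3 = 2.7 and 11.175 − 7.85 = 3.3 points.

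**The case against.** The strongest reply is that the sentences can be read together: withdrawals are nonresponders on the primary endpoint, and LOCF fills isolated gaps and the other outcomes. Their positions in the section support this. A reader might infer that the two rules contradict each other, but the text does not go that far. What stands is that the order of precedence is left unstated.

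A reader might also infer that the plan intends to carry scores from one treatment into the other, and that this affects the primary endpoint. The plan does not say so. On the primary endpoint the nonresponder rule already covers patients who leave in period 1. A patient who attends V5 normally has a washout or period 2 value as the last one. The exposure is therefore in the secondary outcomes, where LOCF as worded does not prevent it and where the SF-36 schedule leaves nothing else to carry.

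Finally, the plan names LOCF and does not say that a preferred alternative will replace it, so a results-driven switch is permitted and not announced. The simulation takes *best* to mean most favourable and uses a Wilcoxon test, so it does not measure inflation of the planned log-rank comparison. Both limits are accepted. The objection does not rescue the stated purpose of the sensitivity analyses, which they cannot serve. That is a wrongly stated rule, and more than a detail left to an analysis plan.

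**Conclusion.** The point holds in this form: the plan gives sensitivity analyses a task they cannot perform and so leaves the method open to a data-driven choice; LOCF is not limited to the current period; and its rank against the nonresponder rule is not stated.

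The firmest consequence needs no assumption beyond Table 1: a missing V7 SF-36 score cannot be filled with a period 2 on-treatment value. The other sizes are conditional. The choice of rule could move the lacosamide response rate by 0 to 10 points at 10% dropout, but only if LOCF overrode the nonresponder rule. Selecting the most favourable of three methods could raise a 5% error to about 7.6% at 10% missing per period, and to 10.0% and 11.2% at 20% and 30%, under the simulation assumptions above.

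The documents do not show that the primary result will be wrong or that its error rate is inflated by any known amount. This should be changed before unblinding, and it does not put the design in question.

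**What to change.** Three changes of wording in the Type of analysis section:

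1. Replace the sentence about finding the best method. Name one primary missing-data method, fixed before unblinding, and name multiple imputation as a sensitivity analysis that reports robustness and cannot replace the primary result.
2. Keep withdrawal as nonresponse for the primary endpoint, and state that this rule takes precedence over LOCF.
3. State that no value is carried from one treatment period, its taper or the washout into the other period. A secondary outcome with no on-treatment value in a period is treated as missing for that period.

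LOCF within a period and the planned nonparametric secondary tests can stay. The cost is slightly more analysis work and a few more missing secondary values, SF-36 above all. No visit or patient procedure changes. The article reports recruitment as ongoing and blinding as held to the end of the study, so the change could be made before any treatment code is opened.
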